##### Relevant concomitant care permitted or prohibited during the trial

No restrictions or changes to medications or other treatments, or additional clinic visits are required as part of the REMORA2 trial. Patient participants continue to be followed up and use all medications as prescribed by their care team throughout the study.

##### Provisions for post-trial care

Once a patient participant has completed their final clinic visit in the 12 ± 3-month follow-up window, they are no longer considered to be on trial and are advised in writing that they have completed the study. Those allocated to the intervention group return to receiving standard of care only, and the REMORA app and interactive dashboard will be deactivated. There is no anticipated harm and compensation for trial participation.

#### Assignment of intervention: allocation and blinding

##### Sequence generation

As illustrated in Fig. 1, the 16 clusters are randomly assigned a site letter (A-P) by the programme manager independently of the trial statistician. Using computer-generated simple randomization, the trial statistician independently and randomly allocates letters A-P to eight sequences, numbered 1–8. The numeric order of the sequences reflects the order in which clusters switch over from standard of care to integrated symptom tracking, with sequence 1 switching over after the first 3-week period and sequence 8 at 24 weeks for the eighth and final step.

##### Concealment, implementation and blinding

The list of site names and letter allocations is stored in a password-protected file that only the programme manager has access to. The password-protected list of sequence numbers can only be accessed by the programme manager and trial statistician.

All sites will initially open to recruit to clinic visits offering standard of care. At the end of each 3-week period, the programme manager advises the study team which sequence is due to switch over to clinic visits offering integrated symptom tracking. The study team uses letters rather than site names to refer to clusters during meetings and in documentation to ensure the trial statistician remains blinded to the clusters’ identities. Similarly, the trial statistician is blinded to allocation of individual participants. Together, this reduces the risk of undue influence on the analyses and interpretation of results. The trial statistician remains blinded until the end of the REMORA2 trial when the primary and secondary outcome analyses have been completed. We do not foresee any circumstances or procedures that would require revealing a cluster’s or participant’s allocation to the trial statistician.

To reduce the risk of recruitment bias, clusters are not informed of their time of switch over from standard of care to integrated symptom tracking. This means that, until the first patient-reported symptom data appears in the interactive dashboard in the electronic health record, patients approached to participate cannot be informed by the site at the time of recruitment about whether their hospital is currently offering clinics with or without integrated symptom tracking. Where plausible, site team members who are not directly responsible for patient care but are involved in recruitment are kept unaware of the current intervention type being offered until the end of the recruitment period.

As it is not possible to blind patients from the intervention, they receive information about their allocation upon consenting to take part; allocation is managed by the study team. Patient-facing materials have been designed to present the control and intervention conditions in equipoise as much as possible to minimize influence on treatment beliefs. Similarly, it is not possible to blind healthcare professionals directly responsible for patient care due to patient-reported symptom data becoming available in the interactive dashboard once patient participants start tracking as part of the intervention.

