### Statistical methods

#### Statistical methods for primary and secondary outcomes

This section summarizes the planned statistical methods for the primary and secondary quantitative outcomes listed in Table 1. For all analyses described below, we will take an intention-to-treat approach, i.e. we will include participants in the treatment group they are assigned to regardless of the extent to which they take up or adhere to the intervention. Further details, including on methods for qualitative outcomes, will be provided in the full statistical analysis plan, which we will draft with input from the trial’s programme steering committee and publish before we lock the trial data set.

We will report the trial results in accordance with the CONSORT stepped wedge trial extension [60].

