### Oversight and monitoring

#### Composition of the coordinating centre and trial steering committee

The coordinating centre is at the University of Manchester, where most of the study team is also based. There are three internal oversight groups. First, the REMORA2 programme management group comprises individuals responsible for the day-to-day management of the trial, as well as at least one member of the PPIE group. They meet monthly to monitor management of the programme, progress across workstreams, communications, trial outputs and future plans. Second, the REMORA2 trial management group, a subgroup of the programme management group, meets monthly to monitor all aspects of the conduct and progress of the trial, ensure protocol adherence and take appropriate action to ensure the quality of the research. Lastly, the scientific committee includes all study team members responsible for the scientific integrity of the trial, complemented with a PPIE group representative. This committee meets monthly to discuss methodological challenges (e.g. with data analysis), review preliminary findings, present recent advances in the field of integrated symptom tracking and provide oversight of publications in draft.

Furthermore, we have established the REMORA2 programme steering committee. It has external representation from an independent chairperson, one other independent expert, an independent statistician with stepped wedge trial expertise and one independent patient representative. It additionally has internal representation from the co-principal investigators and the programme manager. Other invitees may include a PPIE group member, study team members, a sponsor representative, or funder representatives, as needed. The committee meets at least twice annually.

Lastly, we have convened an independent expert group that meets once every 9–12 months to advise on future implementation and scalability of integrated symptom tracking beyond the REMORA2 trial. Membership includes representation of patient and professional organizations, commissioners, healthcare providers, digital health industry, academia and guideline and regulatory bodies.

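### The claimed blind of the trial statistician to participants' allocation does not fit the described design, because the statistician generates and can open the list that fixes each cluster's switch date

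*Protocol article*

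**What the plan says.** Under Concealment, implementation and blinding, the article makes two claims about the trial statistician. The first is a blind to which hospital each letter stands for, kept by using letters in meetings and documents. The second concerns participants: "Similarly, the trial statistician is blinded to allocation of individual participants". The two together are presented as reducing undue influence on the analyses. The stated duration is long: "The trial statistician remains blinded until the end of the REMORA2 trial when the primary and secondary outcome analyses have been completed". The section adds that no foreseeable circumstance or procedure would reveal a cluster's or a participant's allocation to the statistician.

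Under Sequence generation, "the trial statistician independently and randomly allocates letters A-P to eight sequences, numbered 1–8". The meaning of those numbers is also given: "The numeric order of the sequences reflects the order in which clusters switch over from standard of care to integrated symptom tracking". The first sequence changes over at week 3 and the last at week 24. On access, the blinding section says: "The password-protected list of sequence numbers can only be accessed by the programme manager and trial statistician". The only list kept from the statistician is the one linking site names to letters.

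Under Trial design, a participant's arm depends on the period of recruitment; there is no individual randomization. The primary model includes intervention and a random effect for cluster. The SAP is still to be drafted, and its stated timing is to "publish before we lock the trial data set".

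**The concern.** In this design a participant's arm is a function of two things: the cluster's sequence and the recruitment period. A person who holds the letter-to-sequence list already has the first for every letter. Replacing hospital names by letters hides the hospital but not the arm, because the list is keyed on those same letters.

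Patients and treating professionals cannot be blinded here, so readers will give weight to a statement that the analyst was. Several choices are left to the SAP: the further prognostic covariates, the imputation model, and any sensitivity analyses added if the missing-data assumption comes into doubt. A blind analyst would be one protection against making those choices with the results in view. An SAP fixed before outcomes are seen would be another. The first is not supported by the described arrangements, and for the second the article states only that publication precedes data lock.

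**Working it through.** **Inputs.** 16 clusters, 8 sequences of two clusters, one switch every 3 weeks, 27 weeks of recruitment (Trial design, Fig. 1 caption and Sequence generation); 46 participants per site (Sample size). Even accrual over time is my assumption.

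**Reproducing the schedule.** Last switch: 8 × 3 = week 24. Number of periods: 8 + 1 = 9. Recruitment: 9 × 3 = 27 weeks. Both figures match the article.

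**Rule for arm.** A participant recruited in period p at a cluster in sequence k is in the intervention arm if p > k, and otherwise in control.

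**Case 1: list, letter and recruitment period known.** There are 16 × 9 = 144 cluster-periods. The rule settles all 144 (72 control, 72 intervention), so every participant's arm follows.

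**Case 2: list and letter known, arm shown only as code A or B, no dates.** The model needs cluster and an arm variable, so these are the least the analyst must have. A cluster in sequence k has k control periods and 9 − k intervention periods, so its intervention share is (9 − k)/9.
- Sequence 1: 8/9 intervention. With 46 participants, 46 × 1/9 ≈ 5 control and 46 × 8/9 ≈ 41 intervention.
- Sequence 8: 1/9 intervention, or about 41 control and 5 intervention.

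The code that dominates in the early-switching letters is the intervention. Once that is known, every participant's arm is known. Accrual would have to be very uneven across all the sequences to hide this.

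**Case 3: recruitment date known, no list.** Everyone in period 1 is control and everyone in period 9 is intervention: 16 + 16 = 32 of 144 cluster-periods, or 22%. In period p the share of clusters on intervention is (p − 1)/8, so guessing the commoner arm is right with frequency 1, 7/8, 6/8, 5/8, 4/8, 5/8, 6/8, 7/8, 1 over the nine periods. The sum is 7, and 7/9 = 78%. Withholding the list alone therefore weakens the inference but does not give a full blind.

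**Case 4: cluster codes re-keyed, arms coded, no list and no dates.** Under even accrual the set of shares 1/9, 2/9, …, 8/9 is unchanged when A and B are swapped, so the split no longer identifies the arm. This is the arrangement under which the claim could hold. The article describes neither re-keying nor withholding of dates.

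**The case against.** The strongest reply is that unblinding is inferred, not stated. The listed model terms include follow-up length, which is a duration, and no period term, so the statistician need not receive recruitment dates. With re-keyed codes and no dates, coded arms would stay masked (Case 4). That is right as far as it goes, and it means Case 1 is conditional on what the statistician is given. It does not rescue the text. Letters are the described working label, no second set of codes is mentioned, and with the letters and the list Case 2 needs no dates.

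It can also be said that much is already fixed: one primary outcome, baseline adjustment, a random cluster effect, intention to treat, multiple imputation with a complete-case sensitivity analysis, and SAP input from a steering committee that includes an independent statistician. Publication before lock does not exclude an earlier freeze. All of this stands and limits what is at stake.

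A reader might go further in three ways that the article does not support.
- That the statistician works on accruing outcomes while the SAP is open. No section says the statistician sees outcomes before lock, and no interim analysis is planned.
- That the internal scientific committee's remit to "review preliminary findings" means results by arm. It sits in a list of general business, and the trial also has a process evaluation with findings of its own.
- That app and dashboard usage data, which exist in one arm only, unmask the analyst through the engagement sensitivity analyses. Those are described as assumed scenarios and do not cite usage data; Table 1 assigns usage data to descriptive analysis.

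**Conclusion.** The statement that the statistician is blind to clusters' and participants' allocation until the analyses are complete contradicts the arrangements in the same part of the article. At letter level the statistician created the cluster allocation, and individual allocation follows from it. With the list, arm is derivable in 144 of 144 cluster-periods from letter and period, and coded arms can be decoded from letter and code alone under roughly even accrual. The blind to hospital identity is supported; the blind to allocation is not.

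This rests on two assumptions: that the trial statistician carries out or directs the analysis, as the purpose given for the blind implies, and that the analysis data carry the letters A–P or a code traceable to them. It would be too strong to say that analysis choices have been or will be driven by data, or that no protection exists. The conclusion is that a stated safeguard is not delivered as described, and that the article gives no date earlier than data lock for fixing the SAP. The point should be corrected; it does not invalidate the design.

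**What to change.** In Concealment, implementation and blinding, choose one of two courses.

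(a) Limit the claim: say that the statistician is blind to site identity only, and remove the statements that individual and cluster allocation stay hidden. Then, under Statistical methods for primary and secondary outcomes, replace the data-lock deadline by sign-off and posting of the SAP before any follow-up outcome data are released to the statistician.

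(b) Make the claim true: have someone other than the analysing statistician generate and hold the sequence list, and supply the analysis data with re-keyed cluster codes, coded arms and no recruitment dates. Say plainly that dates alone would still fix the arm in the first and last periods (22% of cluster-periods). If the SAP adds a calendar-time term that needs dates or ordered periods, this course cannot give a full blind and (a) is the safer choice. Where the present statistician has already generated the list, (b) also needs a different analyst, or re-keying by someone else before any data transfer.

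Course (a) costs a less favourable blinding statement and an earlier SAP deadline. Course (b) costs a second person's time and a data-preparation step. Neither alters recruitment, treatment or data collection.

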#### Strategies to improve intervention uptake and adherence (i.e. intervention fidelity)

The REMORA2 trial employs several strategies to promote participants’ uptake of and adherence to the interventions. These have been informed by the findings from our feasibility trial [32], as well as by our patient and public involvement and engagement (PPIE) group. We describe the trial’s PPIE activities and outcomes to date below before providing further details on the promotional strategies.

##### Strategies for patient participants

Patient participants allocated to the intervention group will receive a mix of (up to five) e-mail and telephone call reminders about downloading, setting up and submitting their first symptom report using the REMORA app. Throughout the trial, they can request technical and other support via a telephone and email helpdesk during office hours; this includes peer support offered via the PPIE-led helpdesk.

Once patient participants have started using the app, they receive in-app reminders for submitting their daily/weekly/monthly reports. Patient participants who are not engaging with symptom tracking (defined as submitted < 50% of daily symptoms in the 14 days after tracking commenced, and monthly thereafter) receive (up to five) further email reminders.

##### Strategies for healthcare professionals

We provide physical reminders for healthcare professionals to review patient-reported symptom data using the interactive REMORA dashboard and collect the primary outcome data. This includes a Disease Activity Score for 28 joints (DAS28) desktop assessment tool, paper case report forms (CRFs) with REMORA2 logo, and REMORA pens and stickers. We also invite healthcare professionals to wear a REMORA-branded lanyard and pin badge to help patient participants mention their involvement in the study when they have a clinic visit (see Figure S4 for a photo of REMORA-branded materials). Where possible, clusters incorporate locally tailored reminders, such as flagging patients’ participation in outpatient letters or in electronic health records.

### Participants

#### Eligibility criteria

There are five participant groups: (1) Healthcare professionals participating in the trial, (2) Patients participating in the trial, (3) Eligible healthcare professionals who decline trial participation, (4) Eligible patients who decline trial participation and (5) Professionals or volunteers involved in implementing integrated symptom tracking. All should be willing and able to provide full informed consent. We summarize further eligibility criteria for each group below and in supplementary Table S3.

##### Healthcare professionals participating in the trial

Healthcare professionals are eligible to take part in the REMORA2 trial if they are (a) responsible for the assessment and treatment of people with RA, (b) have access to the hospital’s electronic health record system as part of routine care delivery and (c) are willing to review the interactive REMORA dashboard during clinical visits with consented patients in the intervention group.

Healthcare professionals taking part in the trial can also participate in an interview and/or clinic observations as part of the process evaluation if they are willing.

##### Patients participating in the trial

Adult patients (18 years or older) are eligible to take part in the REMORA2 trial if they (a) are under the care of a consented healthcare professional, (b) have active probable/definite RA (see Table S3 for definition), (c) have regular access to an app-compatible, internet-connected mobile device and a valid email address, (d) are able to follow the intervention set-up instructions independently or with support (see ‘ Intervention description’ for details), (e) have a record with clinical data in the regional data repository (see element 4 in Fig. 2) and (f) speak and understand English, or are supported by someone who does.

Patients taking part in the REMORA2 trial can also participate in an interview and/or clinic observation as part of the process evaluation, if they are willing and did not previously participate in the feasibility trial [32].

##### Eligible healthcare professionals who decline trial participation

Healthcare professionals who are a member of the care team in one of the clusters and are eligible but decline to take part in the trial, are eligible for an interview as part of the process evaluation if they are willing.

##### Eligible patients who decline trial participation

Patients who are eligible but declined to participate in the REMORA2 trial are eligible for an interview as part of the process evaluation, if they are willing, regardless of whether they previously took part in the feasibility trial [32].

##### Professionals or volunteers involved in the implementation of integrated symptom tracking (implementers)

Healthcare professionals, other professionals (e.g. IT staff, information governance experts), or volunteers are eligible for taking part in an interview for the process evaluation if they have been involved in the technical and/or organizational implementation of the REMORA2 intervention (i.e. integrated symptom tracking) at a local (e.g. hospital), regional (e.g. data repository) or national (e.g. NHS login) level. We will refer to this participant group as ‘implementers’ in the remainder of the manuscript.

#### Recruitment

##### Healthcare professionals

Trained and delegated members from teams within clusters are responsible for recruitment, supported by the study team. Healthcare professionals are primarily recruited prior to patient recruitment commencing (see Fig. 1), with further recruitment taking place throughout the REMORA2 trial as needed (e.g. due to staff changes). All eligible healthcare professionals receive training from the study team on how to use the interactive REMORA dashboard (see ‘ Intervention description’), as well as a participant information sheet with adequate time to consider if they wish to participate, and the opportunity to ask further questions.

Those declining trial participation who provided consent to be contacted (see ‘ Informed consent’) receive an invitation for the process evaluation by taking part in an interview, covered in a separate participant information sheet.

##### Patients

Potentially eligible patients are primarily identified via case note review by trained and delegated members from teams within clusters. Localized recruitment posters displayed in patient areas advertise the REMORA2 trial to people who have not yet been approached, and healthcare professionals have localized REMORA ‘business cards’ they can give to patients who may be eligible and interested. The posters and cards include a URL and QR code leading to the study website [38], as well as details for whom to contact for expressing an interest or for more information.

Following identification, cluster team members approach patients in-person in clinic, by telephone, or via mail to discuss the trial and confirm eligibility via a brief screening procedure. Interested individuals receive a participant information sheet (available on [40]). with adequate time to consider if they wish to participate, and the opportunity to ask further questions. To ensure adequate patient participant enrolment, all cluster teams receive weekly calls from the study team to discuss and address any recruitment barriers, monthly newsletters with updated cluster-level recruitment numbers compared to targets, and site visits from the programme manager to identify further recruitment opportunities as required.

Patients declining trial participation who provided consent to be contacted (see ‘ Informed consent’) receive an invitation for the process evaluation by taking part in an interview, covered in a separate participant information sheet.

